## Abstract

**Background:**

In France, emergency departments (EDs) are the fastest and most common means for general practitioners (GPs) to cope with the complex issues presented by elderly patients with multiple conditions. EDs are overburdened, and studies show that being treated in EDs can have a damaging effect on the health of elderly patients. Outpatient care or planned hospitalizations are possible solutions if appropriate geriatric medical advice is provided. In 2013, France’s regional health authorities proposed creating direct telephone helplines, “geriatric hotlines,” staffed by geriatric specialists to encourage interactions between GP clinics and hospitals. These hotlines are designed to improve health care pathways and the health status of the elderly.

**Objective:**

This study aims to describe the health care pathways and health status of patients aged 75 years and older hospitalized in short-stay geriatric wards following referral from a geriatric hotline.

**Methods:**

The study will be conducted over 24 months in seven French university hospital centers. It will include all patients aged 75 and older, living in their own homes or nursing homes, who are admitted to short-stay geriatric wards following hotline consultation. Two questionnaires will be filled out by medical staff at specific time points: (1) after conducting the telephone consultation and (2) on admitting the patient to a short-stay geriatric medical care. The primary endpoint will be mean hospitalization duration. The secondary endpoints will be intrahospital mortality rate, the characteristics of patients admitted via the hotline, and the types of questions asked and responses given via the hotline.

**Results:**

The study was funded by the National School for Social Security Loire department (École Nationale Supérieure de Sécurité Sociale) and the Conference for funders of prevention of autonomy loss for the elderly of the Loire department in November 2017. Institutional review board approval was obtained in April 2018. Data collection started in May 2018; the planned end date for data collection is May 2020. Data analysis will take place in the summer of 2020, and the first results are expected to be published in late 2020.

**Conclusions:**

The results will reveal whether geriatric hotlines provide the most effective management of elderly patients, as indicated by shorter mean hospitalization durations. Shorter hospital durations could lead to a reduced risk of complications—geriatric syndromes—and the domino chain of geriatric conditions that follow. We will also describe different geriatric hotlines from different cities and compare how they function to improve the health care of the elderly and pave the way toward new advances, especially in the organization of the care path.

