The aims of this study are to describe and compare how the geriatric medicine hotlines function with the goal of standardizing their use and defining ways they can be improved. We will also analyze the principal responses provided to GPs who call the hotlines and improve awareness of this tool. We hypothesize that geriatric hotlines will lead to reduced mean durations of hospitalizations by helping prevent time spent in EDs when it is unnecessary and potentially a risk. Through the use of a direct geriatric hotline diagnostic tool, we believe elderly patients will experience better health care pathways that no longer involve multiple trips to EDs. The hotlines may facilitate better adapted and more appropriate responses to situations that do not necessarily need hospitalization and provide better alternatives (eg, therapeutic medical and social care, outpatient care, consultations, ambulance services, telemedicine).

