### Participants

The study population will be people aged 75 years and older, living in their own home or a care facility (including independent-living facilities), hospitalized in short-stay geriatric care and referred by the hotline in one of the investigating centers. All participants will be fully aware of the study and their rights regarding their participation. All participating patients will give their consent. Participants or a legally authorized representative will receive informational brochures and give their informed oral consent (more visual difficulties and writing for the elderly). All participants will be able, at any moment and by any method, to withdraw from the study.

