## Discussion

This study will enable us to determine whether a geriatric hotline offers effective management of elderly patients. Could planned hospitalizations be the best solution for our elderly? Will this approach lead to less geriatric syndromes [4-10]?

Wargon et al [4] demonstrated that the elderly spend more time in EDs, which is a potential source of dysfunction in the organization care offered by these services and lowers chances of positive outcomes for the patient. Therefore, there is interest in enabling the assessment of geriatric health status to limit visits to EDs as much as possible and improve the care pathways offered to elderly patients. In a retrospective study, Mazière et al [8] demonstrated that elderly admissions to EDs are independently associated with functional decline in terms of daily activities. The findings of these studies indicate that improving interactions between GP care and hospital services could enable more direct referrals of patients to multidisciplinary care in short-stay geriatric wards, consequently improving the functional prognosis of elderly patients and avoiding geriatric syndromes secondary to ED care.

The study has several strengths. It is a multicentric study covering a large patient sample. The diversity of the participating investigating centers (across three different regions) and their populations is also likely to offer diverse responses. Is the time spent in ED consultations greater in the larger centers? Does this lead to more cases of geriatric syndrome? Are there closer, more effective ties between GP clinics and hospitals in areas with a lower population density? Do these areas (with a lower population density) benefit from better understanding and communication of this type of care? The analysis will be conducted across subgroups (town by town) to avoid confusion bias. The overall population will be sourced from different types of regions (ie, rural, semiurban, urban) to reveal whether this factor has an impact on the knowledge of or access to the hotline [24]. The analysis will enable evaluation of GP clinic-hospital interactions [25] according to population centers, and the need for links between these health care areas, to determine the strengths and limitations and to reinforce GP clinic and hospital collaboration with the aim of reducing ED admissions [26].

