Another advantage of our study is its innovative character because there are currently very few studies analyzing geriatric hotlines [25]. In addition, it is observational in nature, which enables many types of procedures from across the country to be analyzed, leading to more standardized approaches.

The study does have limitations, notably its nonrandomized nature. There is no comparison because it is a descriptive study. The quality of the responses will be operator-dependent. Eventually, the goal will be to conduct a second study aiming to compare profiles of elderly patients hospitalized in short-stay geriatric wards via EDs versus those referred via a geriatric hotline. Through the first questionnaire, we will analyze the different responses provided by the hotline (eg, call-outs, consultations, telemedicine, day hospital). We will evaluate the number of hospitalizations avoided or deferred in time following the use of the hotline to reduce inappropriate passage through EDs.

This first study will demonstrate if managing patients by means of a geriatric hotline offers the most effective approach and results in shorter mean hospitalization durations and thus fewer complications and geriatric syndromes and fewer trips to EDs. It will also describe and compare the function of different geriatric hotlines across France to improve health care pathways for the elderly and pave the way toward future advances, such as new modalities of patient management, the development of more appropriate responses to this population, and the reduction of inappropriate visits to emergencies, which we know can be deleterious for the elderly.

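### The protocol promises a verdict on whether hotlines are the most effective management, but it enrols hotline-referred patients only and itself says there is no comparison

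*Protocol article*

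**What the plan says.** All references are to the protocol article.

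**What it promises**
- Abstract, Conclusions: "The results will reveal whether geriatric hotlines provide the most effective management of elderly patients, as indicated by shorter mean hospitalization durations".
- Discussion, opening: "This study will enable us to determine whether a geriatric hotline offers effective management of elderly patients".
- Discussion, closing paragraph: "This first study will demonstrate if managing patients by means of a geriatric hotline offers the most effective approach". The same sentence continues to shorter mean stays and "thus fewer complications and geriatric syndromes and fewer trips to EDs".
- Introduction: "We hypothesize that geriatric hotlines will lead to reduced mean durations of hospitalizations". The Discussion adds a second hypothesis, that planned admissions have shorter stays.

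**What it sets up**
- Abstract, Objective: "This study aims to describe the health care pathways and health status of patients".
- Participants: people "hospitalized in short-stay geriatric care and referred by the hotline in one of the investigating centers".
- Evaluation Criteria: the primary endpoint is the mean stay on the short-stay geriatric ward.
- Statistical Analysis: hotline patients are compared by sex and by type of discharge, with results overall and by center.
- Discussion, limitations: "There is no comparison because it is a descriptive study". A later study is to compare the profiles of ED-admitted and hotline-referred patients.

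**The concern.** The protocol gives its primary endpoint a reading that the endpoint cannot carry. A single-group mean says how long hotline-referred patients stayed. It does not say whether they stayed less time than they would have by another route, or whether the hotline is better than any alternative. The claim appears in the abstract and twice in the Discussion, and its last appearance comes in the paragraph directly after the statement that no comparison exists. A reader of the abstract alone would expect a comparative result.

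The closing sentence goes a step further, treating shorter stay as evidence of fewer complications, geriatric syndromes and ED trips. That would need those events to be observed in the patients, which is not how the data collection is described.

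**Working it through.** The protocol gives no figure for a hotline contrast (no effect size, SD or power), so there is nothing of its own to reproduce. The check sets the sections side by side.

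**1. What the claim needs.** Let D = (mean stay, hotline) − (mean stay, ED route). *Shorter* means D < 0. The study observes the first term only. Suppose it found a mean of 11.6 days. If ED-admitted patients in the same hospitals averaged 14.1 days, D = 11.6 − 14.1 = −2.5. If they also averaged 11.6, D = 11.6 − 11.6 = 0. The study's data are the same in both cases. (These two figures are borrowed from the study cited in the Discussion, for illustration only.)

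**2. Is there a comparator inside the study?** Four places to look:
- *Selection criteria.* These omit hotline referral. But Participants requires it, and Recorded Variables has the second questionnaire completed after hotline referral. No control group follows from the omission.
- *Centers.* Design and Setting requires each center to have a dedicated doctor-to-doctor line. Comparing centers therefore compares one hotline with another.
- *Admission route.* The items listed for the patient questionnaire include no route (direct, through the ED, planned).
- *Call form.* Emergency versus deferred admission is recorded there, but Recorded Variables says the form carries no identifier. As described, it cannot be linked to a patient's stay, so the planned-admission hypothesis cannot be tested either.

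**3. Does a large sample help?** Half-width of the 95% interval for one mean = 1.96 × SD / √n. The protocol gives no SD, so 6 to 15 days is assumed. With 7 centers × 250 = 1750 patients:
- SD 6: 1.96 × 6 / √1750 = 0.28 days
- SD 15: 1.96 × 15 / √1750 = 0.70 days

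With an assumed intra-center correlation of 0.05, the design effect is 1 + 249 × 0.05 = 13.45 and the effective n is 1750 / 13.45 = 130. The half-widths become 1.03 and 2.58 days. Whichever applies, it describes the first term of D and says nothing about the second. (The protocol's stated total is 2000, which differs from 7 × 250; that is a separate matter.)

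**4. Outcomes in the closing Discussion sentence**

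| Outcome | Where it appears in the listed data | Usable as a patient outcome? |
|---|---|---|
| Length of stay | Primary endpoint; patient questionnaire | Yes, but one group only |
| Complications in hospital | Not listed | No |
| Geriatric syndromes | Falls as history or admission reason; confusion as admission reason | No; not new events during the stay |
| ED trips | Call form, as reason for calling and as response | No; anonymous and call-level |

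Study Endpoint ends participation at ward discharge, so later ED visits are not seen.

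**The case against.** The strongest reply is that the working parts of the protocol are honest. Objective, design, endpoint and tests are descriptive, the limitation is disclosed, the comparison is deferred, and no planned analysis sets hotline against ED. On this view the trouble is a few forward-looking sentences. That stands as far as it goes, and it is why the remedy is confined to wording. It does not remove the contradiction, because the effectiveness claim is restated straight after the limitation.

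A second reply is that a journal article condenses fuller questionnaires, which may hold more variables. This weakens the point about unrecorded outcomes. It does not touch the missing comparator, which the article states outright.

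Some stronger readings are tempting but unsupported:
- *That the study fails to record the outcome in its headline claim.* The abstract sentence names only mean stay, which is the primary endpoint and is recorded. In the abstract, complications and syndromes follow in a separate, hedged sentence; only the Discussion's closing paragraph states them as a consequence.
- *That no ED information is collected.* ED requests and ED referrals are recorded for each call.
- *That ADL at discharge is a missing outcome.* None of the contested conclusions names it. Death and discharge destination are recorded.
- *That the 11.6 and 14.1 days will serve as a historical control.* They are cited as background, and nothing in the analysis plans such a use.

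**Conclusion.** The point holds for the conclusions, not for the data collection or the planned descriptive analyses. As written, the abstract's Conclusions and the opening and closing of the Discussion promise a finding on effectiveness that a study of hotline-referred patients alone cannot give. The hotline-versus-ED difference is not estimable, whatever the sample size. This rests on the article's own statement that there is no comparison and needs no assumed figure; the SDs and intra-center correlation used above only illustrate that precision is beside the point.

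The inference to fewer complications, syndromes and ED trips is also unsupported at patient level. That part assumes that the variable lists in the article are complete.

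**What to change.** 1. In the abstract's Conclusions and in the opening and closing of the Discussion, replace the effectiveness sentences with text such as:

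> *The study will estimate mean length of stay, in-hospital mortality, discharge outcome and patient profile among patients admitted after hotline referral, overall and by center. It will describe and compare how the hotlines function and the responses they give. It will not support conclusions on effectiveness, or on shorter stay relative to ED admission.*

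2. Delete from the closing paragraph of the Discussion the step to fewer complications, geriatric syndromes and ED trips.
3. State that the reduced-duration hypotheses in the Introduction and Discussion are not tested here and need a later comparative study with length of stay as an outcome. The follow-on study now described would compare patient profiles; duration is not mentioned.
4. Present the planned count of hospitalizations avoided or deferred as a description of call-level responses, not as a demonstrated reduction.

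The cost is a less favourable stated conclusion. Data collection and conduct stay as they are.

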**Trial Registration:**

ClinicalTrials.gov NCT03959475; https://clinicaltrials.gov/ct2/show/NCT03959475

**International Registered Report Identifier (IRRID):**

DERR1-10.2196/15423

## Introduction

The world’s populations are aging, which represents a serious public health issue. There are many consequences categorized into four main types: (1) demographic, with increasing numbers and proportions of people older than 65 years with increased life expectancy; (2) epidemiologic, with an accumulation of chronic diseases, incapacitating conditions, and disabilities; (3) economic, with increased health costs and accelerated health care reforms; and (4) social.

The organizational model of hospitals is one of the first elements to be affected by population aging. Over time, the elderly will become the central focus of all hospitals. But how will these establishments address this issue? In France, emergency departments (EDs) are the fastest and most common means for general practitioners (GPs) to cope with the complex issues presented by elderly patients with multiple conditions [1,2]. These services are already overwhelmed, and studies show that being treated in EDs can have a damaging effect on the health of elderly patients [3]. These emergency services can be traumatizing for the elderly and cause the many different complications that are commonly grouped together as “geriatric syndromes” [4-10]. When treated in EDs, the elderly are at higher risk of functional decline due to falls, drug iatrogenesis, and incontinence [11-13].

For emergency physicians, treating elderly patients with multiple pathologies, who often arrive alone, proves to be challenging. Treatment is rendered even more difficult by the lack of time emergency physicians have at their disposal due to EDs being more and more overburdened.

Studies have reported that in 20% to 35% of cases, there was no real need for admission to EDs, and outpatient care or planned hospitalizations would have been possible if appropriate geriatric care was available [14]. Therefore, nearly a quarter of these hospitalizations could have been anticipated and prevented. Some studies on hospitalization durations report that patients with initially planned hospitalizations seem to experience longer times being seen and treated in EDs. Furthermore, this significant number of hospitalizations creates financial issues. According to the French High Council for the Future of Health Insurance, an estimated €2 billion are lost due to the segmentation and inadequacy of response, along with unnecessary hospitalizations [15]. Overall, the literature highlights the need to better coordinate outpatient care with hospital services to provide the elderly with access to more effective care [16].

To improve interactions between GP clinics and hospitals, France’s regional health authorities first organized the area as a unit focused on hospital centers incorporating both EDs and short-stay geriatric wards enabling immediate admission. In parallel, the regional health authorities created telephone hotlines designed to enhance GP clinic-hospital interactions with the aim of reducing the number of hospitalizations, particularly by improving the quality of response. The desired outcome was to improve both the care pathways and health status of the elderly. This hotline service was a recent creation (2013) and is still in an experimental form and not yet widespread. Its use still varies widely across the country, and we have yet to gauge its real value.

The primary objective of this study is to describe the health care pathways and status of patients aged 75 years and older hospitalized in short-stay geriatric care and referred via the hotline. The study population will be from different geriatric care hotlines from around France.

The aims of this study are to describe and compare how the geriatric medicine hotlines function with the goal of standardizing their use and defining ways they can be improved. We will also analyze the principal responses provided to GPs who call the hotlines and improve awareness of this tool. We hypothesize that geriatric hotlines will lead to reduced mean durations of hospitalizations by helping prevent time spent in EDs when it is unnecessary and potentially a risk. Through the use of a direct geriatric hotline diagnostic tool, we believe elderly patients will experience better health care pathways that no longer involve multiple trips to EDs. The hotlines may facilitate better adapted and more appropriate responses to situations that do not necessarily need hospitalization and provide better alternatives (eg, therapeutic medical and social care, outpatient care, consultations, ambulance services, telemedicine).

## Methods

### Design and Setting

This will be a multicenter descriptive study conducted in seven French investigating centers (including university centers, across three different regions) with subgroup analysis (Table 1). Participating establishments will all be voluntary. To participate in the study, the center must have a specific and separate telephone line for doctor-doctor communications. Only calls originating from health care professionals will be included. The study will last for 24 months (May 2018 to May 2020). The course of the study and its design are presented in Figure 1.

Two questionnaires will be distributed at two distinct time points: after telephone consultation (hotline) and after admission to a short-stay geriatric ward. The first questionnaire will be filled out via the hotline by the geriatric specialist answering the call. A second questionnaire will then be filled out during the patient’s hospitalization by the treating geriatric specialist.

**Table 1 table1:** Description of geriatric care offered by different participating centers.

Paticipating center	Residents, n	Hospital beds, n	Short-stay geriatric care	Postdischarge care	Long-term rehabilitation care	Consultation	Outpatient clinic	Ambulance care	Telemedical consultation
Bordeaux	252,000	3076	x	x	x	x	x	x	x
Clermont-Ferrand	141,400	2136	x	x	x	x	x		
Saint Etienne	171,100	1819	x	x	x	x	x	x	x
Angers	151,500	1445	x	x	—^a^	x	x	x	x
Lyon Sud	513,300	1038	x	x	x	x	x	x	—
Saint Chamond	34,870	710	x	x	—	x	—	x	—
Firminy	16,840	475	x	x	x	x	x	x	—

^a^Service not offered.

**Figure 1 figure1:**
[figure not shown]
Flowchart of the study protocol.

### Participants

The study population will be people aged 75 years and older, living in their own home or a care facility (including independent-living facilities), hospitalized in short-stay geriatric care and referred by the hotline in one of the investigating centers. All participants will be fully aware of the study and their rights regarding their participation. All participating patients will give their consent. Participants or a legally authorized representative will receive informational brochures and give their informed oral consent (more visual difficulties and writing for the elderly). All participants will be able, at any moment and by any method, to withdraw from the study.

